## Methods/Design

### Aim

The aims of the study are to:Evaluate the uptake and clinical use of iFOBT in general practice after targeted courses for GPs in correct use of the test.Estimate the diagnostic value of iFOBT when used on patients presenting with non-alarm symptoms of CRC.Investigate the clinical implications of using iFOBT for case finding in general practice.

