### Setting and study population

The study will be performed in the Central Denmark Region (CDR), which is one of five regions in Denmark. The CDR covers approx. 1.2 million inhabitants, 381 general practices, 836 GPs and 19 municipalities. In each municipality, the GPs are organised in units (except for the GPs in the island municipality of Samsø that are included in the unit of Aarhus). Each unit is headed by a chairman who represents the GPs of the municipality. The GPs in Denmark own their own clinic, and approx. 1550 persons are listed per GP. Clinics operate as either solo practices or partnership practices. Remuneration is based on a mix of capitation (25 %) and fee-for-service (75 %) based on a centrally negotiated collective agreement. The GP acts as a gatekeeper to specialised care in the secondary sector, and the citizens must contact the GP for medical advice unless in case of emergency. Approx. 10–20 % of all consultations in general practice ends up with a referral [38]. Nearly all citizens (99 %) are listed with a specific general practice, and the GP is remunerated on the basis of a contract with Danish Regions and must fulfil certain requirements for waiting time and access. iFOBT is available to Danish GPs only to a limited extent as part of the urgent referral for non-specific serious symptoms that might be cancer [39]. However, no logistic setup is available in general practice regarding ordering and analysing the test.

The study population constitutes the 836 GPs in the 381 general practices in the CDR and the individuals aged 30 years or more who are listed with these practices.

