### Design

The study uses a cluster-randomised stepped-wedge design [40]. This design allows us to roll out the study in large scale and to include all general practices in the CDR.

During the first seven months of the study period, each municipality and their appertaining GPs will be randomly and stepwise included in the study to receive intervention (Fig. 1). The intervention (see details later) consists of sending iFOBT kits and a clinical guideline to the GPs and to offer an optional continuous medical education (CME) session about CRC diagnosis. The invitation to the CME is sent to the chairman of the GP unit who will arrange the date and time of the meeting. The month in which the CME is arranged determines the date of inclusion for each municipality. Thus, the date at which a municipality is included is defined as the first working day of the month in which the CME is planned to be conducted. As the CME component is optional, the GP units can choose not to participate in the CME. These municipalities are included on the first working day in the month after confirmation of non-participation (Fig. 2). The specific date of the CME is flexibly arranged as the CME can be scheduled to take place on any of the first 7 months, depending on the preferences of the GPs in the municipality (in consideration of other arrangements targeting GPs in the municipality, availability of venue, etc.).

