#### Mandatory intervention

On the date of inclusion, each GP in the included municipality receives a starting package consisting of 10 iFOBT kits and a clinical instruction on iFOBT use in general practice and how to order the test through the online WebReq system. Furthermore, educational material on CRC diagnostics and use of iFOBT will be available on a web page announcing relevant news for GPs (www.praksis.dk). The online material will have links to the slides from the CME PowerPoint presentation, the clinical instruction and images of the contents in the iFOBT kits.

Approx. 1 month after inclusion, participating GPs will receive a mail containing: status on number of tests requested from their municipality, number and rate of positive tests, number of general practices in the municipality that have started using the test and status of the total number of iFOBTs requested in the CDR. Furthermore, information on how to get help to get started is provided.

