#### Evaluating the uptake and clinical use of iFOBT in general practice

The frequency of each indication used to order the iFOBT will be assessed using descriptive statistics. The development in rate and frequency of iFOBT use are assessed descriptively by illustrating the dissemination with the relation between time and use of iFOBT. One-way ANOVA is used to test for differences in the development of iFOBT use among different municipalities and among different general practices within each municipality. To facilitate comparison of the general practices, they are divided into: clinics where all GPs attended the CME (all-CME-clinics), clinics where at least one, but not all GPs, attended the CME (colleague-CME-clinics) and clinics where no GPs attended the CME (no-CME-clinics). Actions taken on positive test results are assessed by investigating if patients with a positive iFOBT have been referred to colonoscopy. Actions taken on negative test result are assessed by estimating the rate of patients with a negative test result that are referred for colonoscopy and/or has iFOBT repeated.

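### The three CME-attendance groups differ in practice size by construction and in self-selection, so an unadjusted comparison of iFOBT use between them mixes both with any effect of the lecture

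*Protocol article*

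**What the plan says.** The first aim in the protocol article (Aim) is to "Evaluate the uptake and clinical use of iFOBT in general practice after targeted courses for GPs in correct use of the test". The analysis section on uptake and clinical use names one test: "One-way ANOVA is used to test for differences in the development of iFOBT use among different municipalities and among different general practices", the latter within each municipality. The grouping follows directly. "To facilitate comparison of the general practices, they are divided into" three sets. The first two are "clinics where all GPs attended the CME (all-CME-clinics), clinics where at least one, but not all GPs, attended the CME (colleague-CME-clinics"). The third set, labelled no-CME, holds the practices from which nobody went.

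Four other statements bear on these groups:

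- Randomisation: chance decides the month in which a municipality is offered the course, not who goes.
- Design: the course is optional, and "the GP units can choose not to participate in the CME". A unit that declines is included by a different date rule from a unit that accepts.
- Setting and study population: "Clinics operate as either solo practices or partnership practices". There are 836 GPs in 381 practices.
- Mandatory intervention: every GP gets the kits, the clinical instruction and the online material. On the last, "The online material will have links to the slides from the CME PowerPoint presentation".

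**The concern.** Group membership is decided after randomisation by the GPs and their units. GPs who give time to a lecture on colorectal cancer diagnostics may be those who would have used the test more anyway. Two features of the grouping add to this.

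First, the definition of the middle group requires at least two GPs, so solo practices can only be all-CME or no-CME. Practice size is built into the comparison.

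Second, the no-CME group has two sources: practices whose unit turned the course down, and practices in participating units where nobody went. These may differ in local conditions and in how their inclusion date was set.

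A one-way ANOVA carries no covariates, so it separates none of this. At stake is the reading of the article's only contrast that bears on the lecture. A difference, or its absence, could come from size and motivation alone. The Statistical analysis section also notes that iFOBT use before inclusion cannot be compared with use after it, so the outcome itself gives no baseline that would reveal prior differences.

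**Working it through.** The article gives no effect, sample size or power for this comparison, so there is no figure to reproduce. The check is what the group definitions imply.

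**Inputs from the article.** Mean practice size is 836/381 = 2.19 GPs (Setting and study population). The group definitions come from the section on uptake and clinical use.

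**Inputs assumed.** The article gives no distribution of practice size and no attendance rate. I took each GP's attendance probability p as 0.3, 0.5 and 0.7, and the within-practice correlation of attendance as 0, 0.3 and 0.6 (beta-binomial). Two size distributions with mean 2.19 were used: one plus a Poisson, and a geometric.

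**Step 1: group by practice size.** For a practice of k GPs attending independently, P(all-CME) = p^k, P(no-CME) = (1−p)^k, and P(colleague-CME) = 1 − p^k − (1−p)^k. At p = 0.5:

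| GPs | all-CME | colleague-CME | no-CME |
|---|---|---|---|
| 1 | 50% | 0% | 50% |
| 2 | 25% | 50% | 25% |
| 3 | 12.5% | 75% | 12.5% |
| 4 | 6% | 88% | 6% |
| 5 | 3% | 94% | 3% |

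The zero in the first row holds for every p. The gradient below it depends on the assumptions. For four GPs at p = 0.5, the colleague-CME share falls from 88% to about 63% at correlation 0.3 and about 36% at 0.6.

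**Step 2: mean size by group, one case by hand.** Let size be 1 + Poisson(1.194), p = 0.5, attendance independent.

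- P(all) = 0.5 × exp(−1.194 × 0.5) = 0.275, and P(none) is the same.
- P(colleague) = 1 − 2 × 0.275 = 0.450.
- Mean size in all-CME = 1 + 1.194 × 0.5 = 1.60, and the same in no-CME.
- Mean size in colleague-CME = (2.194 − 2 × 0.275 × 1.60)/0.450, which is 2.93 without intermediate rounding.
- Ratio, colleague-CME to all-CME: 2.93/1.60 = 1.83.

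**Step 3: all 18 combinations** (two distributions, three values of p, three correlations).

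| | all-CME | colleague-CME | no-CME |
|---|---|---|---|
| Mean GPs per practice | 1.2 to 2.1 | 2.9 to 3.7 | 1.2 to 2.1 |
| Solo share | 34 to 84% | 0% | 34 to 84% |

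The colleague-CME to all-CME size ratio runs from 1.4 to 3.0. With equal use per GP and no effect of the lecture, tests per clinic would differ by that factor.

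These runs do not model units that decline. There, practices of every size are no-CME, so the mean size of that group would be pulled towards the regional mean.

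**Step 4: what a rate would and would not repair.** Dividing by listed patients or by GPs removes the mechanical factor in step 3. It does not remove a difference in habits between solo and partnership practices, or self-selection. The article gives nothing from which to size those two.

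**The case against.** The strongest reply is that the article makes no causal claim. The groups are formed to ease comparison, and the Statistical analysis section promises only to evaluate dissemination. That is correct. A reader might infer that the plan sets out to estimate the effect of the CME, but the text does not say so. What stands is that the aim speaks of uptake after courses and the article offers no other contrast on the lecture, so it should state how this one may be read.

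Second, the outcome is described as rate and frequency of use, and a condensed article may leave denominators to an analysis plan. This answers the raw-count factor of 1.4 to 3.0 if a rate is used. It does not answer self-selection, and one-way ANOVA is a stated choice, not an omission.

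Third, the comparison may be meant within each municipality, in which case municipalities that declined contribute no contrast. The sentence order allows that reading, but the grouping sentence does not say it.

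Four stronger readings should not be drawn:

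- Size does not fix the groups. A large partnership is always no-CME where the unit declined, and colleagues may attend together. Only the exclusion of solo practices from the colleague-CME group is certain.
- A mean of 2.19 GPs does not show how common solo or large practices are.
- Access to the slides does not bias the contrast. They are open to all three groups by design, and nothing shows who read them. They make the contrast one of attending on top of the mandatory package, and would dilute a difference.
- Nothing in the article says that a decision on providing the course rests on this comparison.

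**Conclusion.** The point holds in a limited form. Following the plan as written gives differences between CME groups that mix any effect of attending with practice size and self-selection, and the named test adjusts for neither. Three parts rest on the text alone: attendance is not randomised, solo practices are excluded from the colleague-CME group, and the no-CME group as defined has two sources.

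The 1.4- to 3.0-fold factor applies to tests per clinic only. It rests on the assumed size distributions, attendance rates and correlations, on equal use per GP, and on no unit declining. The size and direction of the self-selection component cannot be derived from the article.

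The consequence is confined to this comparison. The diagnostic estimates, the sample-size figures and the stepped-wedge comparison are not affected.

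**What to change.** Keep the practice as the unit. The article does not say that tests can be attributed to individual GPs, and analysing by GP would lose the colleague contrast.

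- **Outcome:** iFOBT use per listed patient aged 30 or more.
- **Exposure:** the three groups within size strata, with solo and partnership practices separate, or the proportion of the practice's GPs who attended. In the solo stratum the comparison is simply attended against not attended.
- **Adjustment:** practice size (still needed among partnerships, given the gradient shown above), time since inclusion, and the practice's own pre-inclusion colonoscopy and urgent-referral rates. The section on clinical implications already plans to estimate both rates before the intervention.
- **Population:** restrict the contrast to municipalities that held the CME, and show declining municipalities separately.
- **Reporting:** an association of attending the lecture on top of the mandatory package, not the effect of the CME.

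The cost is small. Attendance is already registered per GP, and no trial procedure changes. Data collection names a register for colonoscopy but none for urgent referral, so the source of that covariate should be confirmed. The price is a more modest statement about the CME, and residual self-selection remains.

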#### Estimating the diagnostic value of iFOBT in general practice

The total number of performed iFOBTs is assessed, and the number and rates of positive tests are calculated. The overall PPV for CRC in case of iFOBT values ≥50 μg/L is calculated, and the optimal cut-off value for the use of iFOBT on patients presenting non-alarm symptoms of CRC will be investigated by ROC curves using cut-off intervals of 50 μg/L.

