## Background

Colorectal cancer (CRC) is the second most common type of cancer in Denmark and is a leading cause of cancer-related death [1, 2]. In Denmark, approx. 25 % of all new CRC cases in 2013 were diagnosed in stage IV with a 5-year survival of less than 5 % [3]. Considering that CRC is a potentially curable disease when found in earlier stages and that survival is strongly related to stage at diagnosis, these figures underline the importance of increasing the proportion of CRCs diagnosed in early stages.Several initiatives have been made to support a stage shift towards earlier diagnosis of CRC. One important step is screening. Studies show that screening for CRC using faecal occult blood tests may reduce CRC mortality in the screened age group [4–6]. Despite the advantages of screening, 75–80 % of CRC cases must still be found through symptomatic presentation in general practice [7, 8]. Therefore, another important strategy has been to support urgent referral and investigation of patients with CRC alarm symptoms [9–11]. This initiative provides the general practitioner (GP) with the opportunity to refer patients presenting with alarm symptoms of cancer to an urgent colonoscopy. Alarm symptoms include rectal bleeding, change in bowel habits, iron-deficiency anaemia, weight loss and abdominal pain [12]. However, the positive predictive values (PPVs) of alarm symptoms are low (2–8 %). Thus, the GPs must each refer 10–20 patients with alarm symptoms for further diagnostic workup to catch one person with CRC [13–15].

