#### Recommended actions on positive and negative test results

In this study, the iFOBT is used as a ‘rule in test’. An iFOBT value ≥ 50 μg/L is considered as positive and should be followed by urgent referral to colonoscopy. An iFOBT value ≤ 49 μg/L is considered as negative. As CRC has a low prevalence in general practice, a negative test result should not exclude CRC; a negative result should rather serve to guide the GP in the direction of the most appropriate diagnostic strategy. The iFOBT can also be repeated.

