### Analysis of the iFOBT and determination of clinical cut-off

In the Danish screening programme, the iFOBT is analysed on OC-Sensor DIANA (Eiken Chemical Company, Ltd, Japan). In the CDR, the analysis is performed at the Department of Clinical Biochemistry at the Regional Hospital of Randers. All iFOBTs requested from general practice during the study period will be analysed using this existing infrastructure in parallel with the screening samples. iFOBTs are analysed continuously and done by staff blinded to colonoscopic findings.

Studies of iFOBT cut-off values have primarily been conducted in a screening setting [45–49]. The cut-off value in the Danish screening programme is set to 100 μg/L. To our knowledge, no studies have investigated an optimal cut-off value for patients presenting non-alarm symptoms of CRC. Small amounts of blood loss in faeces are normal, but no exact reference level exists [50]. On the other hand, small amounts of blood in faeces may also be indicative of CRC. A low cut-off value for blood in stools increases the number of false positive test results and consequently the number of performed colonoscopies and required resources, whereas a high cut-off increases false negative test results and thereby introduces a risk of delay in the diagnosis [31, 51]. In this study, we set the cut-off value to 50 μg/L. Thus, a value of <50 μg/L will be considered as negative and ≥50 μg/L as positive.

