### Sample size

Each included GP is estimated to request 1–2 iFOBTs per week. This estimate is based on a previous report investigating Danish citizens’ reasons for encounter with a GP [56]. When taking into account that the study is rolled out sequentially and the study period is 1 year, we expect that 33,600 iFOBTs will be performed during the study period. Unpublished data from the Danish screening programme reveal that 6–10 % of performed iFOBTs are positive (≥100 μg/L) depending on age and gender. As this study uses a lower cut-off value (50 μg/L) and the investigated population is symptomatic, we estimate that approx. 10 % of performed tests will be positive. Screening studies have shown that the PPV of having CRC when the iFOBT is positive is approx. 10 % [26, 28, 29]. Therefore, we estimate that 10 % of the patients with a positive test will be diagnosed with CRC. In total, we expect to find approx. 336 CRCs by the use of iFOBT during the study period. Approx. 800 CRCs are annually diagnosed in the CDR. Using an alfa of 0.05 and a power of 0.8, we will be able to show a significant reduction in stage IV cancers from 25 to 16 % of annual CRC. However, as a reduction of this scale is unlikely, the study may be underpowered for this secondary outcome.

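### The optimal cut-off is to be investigated by ROC curves, which carry neither prevalence nor colonoscopies per CRC; yield within each 50 μg/L band would answer the stated question better

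*Protocol article*

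**What the plan says.** All references are to the protocol article.

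- The analysis section on diagnostic value states that "the optimal cut-off value for the use of iFOBT on patients presenting non-alarm symptoms of CRC will be investigated by ROC curves", and specifies "ROC curves using cut-off intervals of 50 μg/L". It gives no criterion for choosing a point on the curve.
- The only PPV for CRC in that section is a single figure: "The overall PPV for CRC in case of iFOBT values ≥50 μg/L is calculated".
- The Outcomes section also lists the PPV for CRC by iFOBT cut-off. It does not say whether this is the PPV at or above each cut-off or the PPV between successive cut-offs.
- The section on recommended actions presents iFOBT as a test to rule CRC in, and cautions about negative results with the words "As CRC has a low prevalence in general practice".
- The section on determining the cut-off says that a low value "increases the number of false positive test results and consequently the number of performed colonoscopies and required resources", and that a high value risks missed cancers and delay. The study uses 50 μg/L; the Danish screening programme uses 100 μg/L.
- The section on clinical implications plans the PPV for serious bowel disease, meaning CRC, inflammatory bowel disease or adenomas above 1 cm.

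**The concern.** The protocol poses the choice of cut-off as a trade between colonoscopies spent and cancers found. The ROC curve plots sensitivity against 1 − specificity. Both are conditional on disease status, so the curve looks the same whether CRC affects 1% or 30% of those tested. The quantity on which the protocol says the choice turns is absent from the one tool it names for that choice.

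The figure that bears on moving from 100 to 50 μg/L is the yield among patients with values of 50-99 μg/L, because they alone are referred under one cut-off and not the other. A PPV at or above 50 μg/L averages this group with patients who have much higher values. A cut-off could then be reported as optimal without the reader seeing what the added referrals yielded. The article expects its results to inform recommendations nationally and internationally, so the basis for any such statement should be visible.

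**Working it through.** **Inputs from the protocol article**
- Number of tests (Sample size): "we expect that 33,600 iFOBTs will be performed during the study period".
- Positivity at ≥50 μg/L (Sample size): "we estimate that approx. 10 % of performed tests will be positive".
- PPV among positives: 10% (Sample size).
- Sensitivity: 80-90%, from screening studies (Background). Applying it to symptomatic patients is an assumption.
- Comparison: alarm-symptom PPVs of 2-8%, and 10-20 patients referred "for further diagnostic workup to catch one person with CRC" (Background).

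**1. The plan's own figure.** 33,600 × 0.10 × 0.10 = 336 CRCs. This reproduces.

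**2. Prevalence among those tested.** CRCs among tested = 336 / sensitivity.
- Sensitivity 80%: 336 / 0.80 = 420; 420 / 33,600 = 1.25%.
- Sensitivity 90%: 336 / 0.90 = 373.3; 373.3 / 33,600 = 1.11%.
- Over a wider assumed range of 60-95%, prevalence is 1.67% to 1.05%.

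**3. What an unweighted rule accepts.** Let D patients have CRC and H not. Lowering the cut-off adds *a* patients with CRC and *b* without. Sensitivity plus specificity rises when a/D − b/H > 0, that is when a/b > D/H, that is when a/(a + b) > D/(D + H). The left side is the PPV of the added patients and the right side is the prevalence among all tested. The break-even PPV is therefore 1.11-1.25%. With one colonoscopy per positive test, this is 1/0.0125 = 80 to 1/0.0111 = 90 colonoscopies per CRC.

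The distance-to-corner rule is no stricter here. At the planned operating point (false positive rate 3,024 / (33,600 − CRCs) ≈ 0.091), its break-even ROC slope is 0.091 / (1 − sensitivity): 0.46 at 80% and 0.91 at 90%. Multiplying by the prior odds of CRC and converting to a probability gives break-even PPVs of 0.57% and 1.01%.

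**4. Comparison.** PPVs of 2-8% correspond to 1/0.08 = 12.5 to 1/0.02 = 50 referrals per CRC; the text beside them says 10-20. The limit of 80-90 lies above both ranges.

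**5. Illustration.** Assumed: sensitivity 90% at 50 μg/L and 85% at 100 μg/L; positivity 10% and 6%. The 6% is the low end of the 6-10% screening range given in the Sample size section.

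| | ≥50 μg/L | ≥100 μg/L | Band 50-99 μg/L |
|---|---|---|---|
| Positive | 3,360 | 2,016 | 1,344 |
| CRC | 336 | 317.3 | 18.7 |
| PPV | 10.0% | 15.7% | 1.39% (72 per CRC) |
| False positive rate | 3,024/33,227 = 0.0910 | 1,698.7/33,227 = 0.0511 | |
| Sensitivity + specificity − 1 | 0.809 | 0.799 | |

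The unweighted rule narrowly picks 50 μg/L. The cumulative PPV falls visibly from 15.7% to 10.0%, but neither figure shows the 1.4% in the band.

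**6. Sensitivity to the assumed positivity at 100 μg/L.** With 6%, 8% or 9% positive, the band holds 1,344, 672 or 336 patients. The rule prefers 50 μg/L once the band contains more than 14.9-16.8, 7.5-8.4 or 3.7-4.2 CRCs. In each case this is the same break-even PPV of 1.1-1.25%.

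**The case against.** The strongest reply is that the fault belongs to a rule the protocol does not state. It says only that the optimum will be investigated by ROC curves. A point on a ROC curve can be chosen with a slope weighted for prevalence and cost, and that would not have this weakness. Such detail is often left to the full protocol or the analysis plan, neither of which is shown. This stands: the point is conditional on an unweighted rule, and the missing rule is not itself a finding.

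Second, prevalence-dependent information is planned. A reader might infer that the protocol offers only the ROC curve, or that its PPVs would hide a poor yield completely. The documents do not support that. PPV by cut-off is a listed outcome, nothing says it must be cumulative, and even a cumulative version drops from 15.7% to 10.0% in the illustration. Given the counts, the band yield follows by subtraction. What remains is that a cumulative figure dilutes the band and that nothing links this outcome to the optimum.

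Third, a reader might infer that the extra colonoscopies at 50 μg/L will find almost nothing. That is not supported either. The illustration rests on assumed sensitivities and on screening positivity, its two index values are close, and the actual band yield is unknown and could be well above break-even. CRC is also not the only finding of value: the protocol plans the PPV for serious bowel disease.

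Finally, the second aim is to estimate diagnostic value, and no binding cut-off recommendation is planned. This limits the consequence but does not make the ROC curve a better match to the question.

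**Conclusion.** The point holds as a mismatch between tool and question. The protocol frames the cut-off as a rule-in decision at low prevalence that weighs colonoscopies against missed cancers, and names for it a method that contains neither prevalence nor colonoscopies per CRC. If a common unweighted rule were applied, the lowest acceptable PPV for added patients would be about 1.1-1.25% (80-90 colonoscopies per CRC), against 2-8% for alarm symptoms.

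This rests on the planning figures of 33,600 tests, 10% positivity and 10% PPV, on a sensitivity of 80-90% carried over from screening, and on one colonoscopy per positive test. It is the limiting case that such a rule would accept, not a prediction. It does not show that 50 μg/L is wrong or that any other value is right. It supports a cheap improvement to the analysis; no data would be lost without it.

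**What to change.** Keep the ROC curve as a description of the test. Base the comparison of cut-offs on the yield within each 50 μg/L band (50-99, 100-149 and so on):
- PPV for CRC, with a confidence interval;
- PPV for serious bowel disease as the protocol already defines it, with a confidence interval;
- added colonoscopies per added CRC when the cut-off moves down by one band.

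State before analysis how these figures will inform any cut-off called optimal, and whether PPV by cut-off in the Outcomes section is cumulative, by band, or both. No acceptable number of colonoscopies per CRC is proposed here; whether to set one is for the investigators.

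The cost is wording and a little extra tabulation. The band figures use the iFOBT values, colonoscopy records and CRC diagnoses already to be collected on test-positive patients. The downside is imprecision in sparse bands. Even in the illustrated 50-99 band the standard error is √(0.0139 × 0.9861 / 1,344) = 0.0032, giving an approximate 95% interval of 0.0139 ± 1.96 × 0.0032, or 0.8-2.0%. Bands with fewer patients will generally be less precise.

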### Data collection

All citizens in Denmark are registered in the Danish Civil Registration System with a unique personal identification number (CPR number). This identification number is used in all national registers and enables accurate linkage between national registers [52]. Statistics Denmark will provide data on socioeconomic and demographic factors [53]. Data on iFOBT value and indications for use of iFOBT will be provided by the Department of Clinical Biochemistry at Randers Regional Hospital through the clinical laboratory information system research database [54]. Data on colonoscopy and comorbidity are extracted from the Danish National Patient Register [55]. Data on CRC diagnosis and disease stage are extracted from the Danish Colorectal Cancer Database.

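### The search for an optimal iFOBT cut-off in 50 μg/L steps cannot examine any threshold below the 50 μg/L already in use

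*Protocol article*

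**What the plan says.** Under Estimating the diagnostic value of iFOBT in general practice, the protocol article plans the overall PPV for CRC at 50 μg/L or more. It adds that the optimal cut-off "will be investigated by ROC curves using cut-off intervals of 50" μg/L.

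The section on analysis of the iFOBT and the clinical cut-off fixes the operating rule: "a value of <50 μg/L will be considered as negative and ≥50 μg/L as positive". The same section explains why the threshold is an open question. To the authors' knowledge, "no studies have investigated an optimal cut-off value for patients presenting non-alarm symptoms of CRC". It notes that "small amounts of blood in faeces may also be indicative of CRC", and that "a high cut-off increases false negative test results and thereby introduces a risk of delay in the diagnosis".

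The Outcomes section lists three items under diagnostic value: numbers and rates of positive tests, overall PPV, and PPV by cut-off. For test-negative patients, the statistical section plans "estimating the rate of patients with a negative test result that are referred for colonoscopy and/or has iFOBT repeated". Under Data collection, the laboratory provides the iFOBT value itself, and "Data on CRC diagnosis and disease stage are extracted from the Danish Colorectal Cancer Database". Records are linked by personal identification number.

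**The concern.** The step width of the grid equals the operating cut-off. Multiples of 50 μg/L are 0, 50, 100, 150 and so on, so nothing lies between calling everyone positive and the threshold already in use. The analysis is described as a search for the optimum, but one side of the current value is closed off before the data are seen.

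This conflicts with the article's own reasoning, which presents the cut-off as a trade between false positives and false negatives and says that small amounts of blood may matter. Whether 50 μg/L is too high for these patients is therefore a question that the article opens and its analysis cannot answer. Estimating the diagnostic value of the test is the second of the three stated aims, and the Discussion expects the results to inform future recommendations. A finding that 50 μg/L is optimal could then be read as evidence against lower values when none had been examined.

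**Working it through.** **Inputs from the protocol article**
- Expected tests: 33,600 (Sample size)
- Expected share positive at 50 μg/L: 10% (Sample size)
- Expected PPV for CRC: 10% (Sample size)
- ROC step: 50 μg/L (Estimating the diagnostic value)
- Operating cut-off: 50 μg/L (Analysis of the iFOBT)
- Sensitivity in screening studies: 80–90% (Background), used only as an illustration

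**Step 1. The plan's own figure.** Tests × share positive × PPV = 33,600 × 0.10 × 0.10 = 336 CRCs. This matches the stated figure of approximately 336.

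**Step 2. The grid.** Candidates at 50 μg/L steps are 0, 50, 100, 150, 200 and so on. None lies strictly between 0 and 50. The point at 0 classes every patient as positive and is no usable threshold.

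**Step 3. Results pooled in the lowest bin.** Positives: 0.10 × 33,600 = 3,360. Results from 0 to 49 μg/L: 33,600 − 3,360 = 30,240, which is 90% of all tests.

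**Step 4. Where the curve stops carrying information.** False positives at 50 μg/L: 3,360 − 336 = 3,024. The false-positive rate is 3,024 / (33,600 − all CRCs among tested patients).
- No missed CRCs: 3,024 / (33,600 − 336) = 3,024 / 33,264 = 9.1%.
- 84 missed CRCs: 3,024 / (33,600 − 336 − 84) = 3,024 / 33,180 = 9.1%.

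The lowest examined threshold therefore sits at about 9% false positives whatever the number missed. From there to 100% the curve is a single straight line, as if the measured values below 50 μg/L did not separate cancers from non-cancers at all.

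**Step 5. How many cancers could lie in that bin (assumption).** Suppose the screening-study sensitivity held here at 50 μg/L. Missed CRCs = 336 / sensitivity − 336.

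| Assumed sensitivity | Missed CRCs among 30,240 negatives |
|---|---|
| 80% | 420 − 336 = 84 |
| 85% | 395 − 336 = about 59 |
| 90% | 373 − 336 = about 37 |

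These are the cancers whose measured values would show whether a lower threshold picks up more disease, and at what cost in false positives. The 50 μg/L grid discards those values. The range of 37 to 84 rests on screening data and is not an estimate for symptomatic patients.

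**The case against.** The strongest defence is that the test is declared to be a rule-in test and that the article says a negative result should not exclude CRC. For that use PPV, overall and by cut-off, is a coherent headline measure. This explains the emphasis in the outcome list, and that emphasis is not a fault. It does not justify the grid: a rule-in test still needs a threshold, and the article promises the optimal one.

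Three stronger readings are tempting, and the document does not support them.

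- **That missed cancers in test-negative patients go unreported.** A ROC curve plots sensitivity against the false-positive rate, so it cannot be drawn without counting CRCs among negatives. The cancer database and the linkage make that possible. What can be said is only that CRC after a negative test is not a named outcome.
- **That sensitivity will be inflated because only positives are steered to colonoscopy.** CRC status comes from a database and not from the index work-up alone. The follow-up window for negatives is not stated, but an article may leave that to the full protocol or analysis plan. Any figure for the inflation would need an assumed fraction of missed cancers that come to light, and the document gives none.
- **That the results are biased towards 50 μg/L.** The grid restricts the choice of threshold. It does not distort the estimates at 50, 100 or 150 μg/L.

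One could also say that the step width is a detail for the analysis plan. Here, however, the article states it explicitly, so it is a choice made and not a choice left open.

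**Conclusion.** The point holds for the grid. As written, the ROC analysis can only confirm 50 μg/L or favour a higher value, although the article calls the optimum unknown and gives reasons to look lower. About 30,240 of 33,600 results (90%) are pooled in one bin, and the curve has no interior point beyond about 9% false positives.

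These sizes rest on the planned volume, the 10% positivity and the 10% PPV, and on reading the intervals as multiples of 50 μg/L, which is the natural reading. The choice of grid does not depend on the assumed sensitivity; only the illustrative 37 to 84 cancers do. It is not shown that a lower threshold would be better, nor that missed cancers are concealed. This is an improvement worth making at almost no cost, and it leaves the rest of the diagnostic analysis intact.

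**What to change.** Build the ROC curve on the measured iFOBT value, or on a fine grid that extends below 50 μg/L as far down as the laboratory reports values (the article does not give that limit). At each threshold, show the sensitivity and specificity that the ROC already produces beside PPV. State that CRC status is taken from the cancer database in the same way for test-positive and test-negative patients.

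No new data source is needed, because the measured value and the linked cancer diagnoses are already in the plan. The cost is a change of analysis wording and a little more analysis work. The change concerns which thresholds are examined; it leaves the operating cut-off and the clinical instruction as they are and recommends no clinical threshold.
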